## Abstract

**Background:**

Few studies demonstrate effectiveness of therapies for oral rehabilitation of patients with cerebral palsy (CP), given the difficulties in chewing, swallowing and speech, besides the intellectual, sensory and social limitations. Due to upper airway obstruction, they are also vulnerable to sleep disorders. This study aims to assess the sleep variables, through polysomnography, and masticatory dynamics, using electromiography, before and after neuromuscular electrical stimulation, associated or not with low power laser (Gallium Arsenide- Aluminun, =780 nm) and LED (= 660 nm) irradiation in CP patients.

**Methods/design:**

50 patients with CP, both gender, aged between 19 and 60 years will be enrolled in this study. The inclusion criteria are: voluntary participation, patient with hemiparesis, quadriparesis or diparetic CP, with ability to understand and respond to verbal commands. The exclusion criteria are: patients undergoing/underwent orthodontic, functional maxillary orthopedic or botulinum toxin treatment. Polysomnographic and surface electromyographic exams on masseter, temporalis and suprahyoid will be carry out in all sample. Questionnaire assessing oral characteristics will be applied. The sample will be divided into 5 treatment groups: Group 1: neuromuscular electrical stimulation; Group 2: laser therapy; Group 3: LED therapy; Group 4: neuromuscular electrical stimulation and laser therapy and Group 5: neuromuscular electrical stimulation and LED therapy. All patients will be treated during 8 consecutive weeks. After treatment, polysomnographic and electromiographic exams will be collected again.

**Discussion:**

This paper describes a five arm clinical trial assessing the examination of sleep quality and masticatory function in patients with CP under non-invasive therapies.

**Trial registration:**

The protocol for this study is registered with the Brazilian Registry of Clinical Trials - ReBEC RBR-994XFS

**Descriptors:**

Cerebral Palsy. Stomatognathic System. Electromyography. Transcutaneous Electric Nerve Stimulation. Phototherapy. Sleep Disorders. Polysomnography.

## Background

Cerebral palsy (CP) refers to disorders of motor development, rising from the primary brain injury, are permanent and changeable character, causing secondary musculoskeletal abnormalities and limitations in activities 
[1]. Recent studies estimate the prevalence of this condition in 2,4 per 1000 children, which means a significant number of people with this kind of disturbances 
[2].

Currently, the children with CP are classified according to their functional independence in gross motor function. Through Gross Motor Function Classification System (GMFCS) for CP 
[3], the classification is by age (0–2, 2–4, 4–6, e 6–12 years), in five functional levels. The system goal is to classify gross motor function with emphasis on the movements of "sit" and "walk" 
[4-6]. Children who have motor function problems similar to those classified at level 1, can generally walk without restrictions but tend to be limited in some of the more advanced motor skills. Children classified at level 5, are usually very limited in their ability to move even with the use of assistive 
[6].

It is known that the main alteration present in children with CP is the motor impairment, which causes several modifications rose from encephalopathy, with consequent changes in body biomechanics. In addition, the child may have intellectual disorders, sensitive, visual and hearing, which added to the motor changes, task constraints and the environment, have repercussions in different ways in their functional performance 
[3,7-11].

Besides the difficulties in locomotion previously described, as a result of the lack of motor coordination, orofacial alterations are also common in these individuals. These disorders are followed by pain, joint noise and irregular or deviated jaw function 
[12]. Individuals with spastic muscles present severely compromised function due to a diminished range of motion, diminished voluntary strength, and increased joint stiffness 
[13].

In general, important functions such as mastication, speech and swallowing are compromised, due to tongue thrusting, cheeks and lips incompetence, resulting in salivary incompetence, presence involuntary bite reflex, asymmetric positioning of the neck, making it difficult to maintain the posture of the head, as well as lack of dynamic balance of the masticatory muscles 
[14-16]. Some therapies may be suggested to treat muscular alteration in CP, such as electrical stimulation, LED therapy and laser therapy 
[17,18]. Neuromuscular electrical stimulation has been proposed as a potentially useful modality for muscle strengthening in children with CP. The electrical neuromuscular stimulation, it is the application of electrical stimulation of sufficient intensity to produce a visible muscle contraction which is applied to the motor point of the muscle, in order to promote muscle strengthening. However, none study that analyzed and compared their effectiveness in adult patients with CP was found so far. Considering the relation between the function of masticatory muscles and the craniofacial complex, the electromyographyc analysis (EGM) is an important tool for the undestanding of muscular pattern when developmental and functional alterations are present 
[19]. Evaluating and treating patients with special needs requires a multidisciplinary approach. In this context, it is important to consider that individuals with CP are also predisposed to sleep-disordered breathing, such as obstructive sleep apnea (OSA), which is one of the most common respiratory disorders. Besides, it could occur oxyhemoglobin desaturation, altered sleep-wake cycle, insomnia, disruption of sleep architecture, thus, resulting in hypoxia events during sleep. Patients with CP have a higher prevalence ranging between 50–60% of sleep-disordered breathing, when compared to individuals without CP. Health professionals should then consider the obstruction of the upper airway during wakefulness and sleep in these patients, since in most cases, OSA is not diagnosed 
[20-22]. In addition, sleep disorder leads to an impairment on mood, behavior, and neurocognitive function and, along with pre-existing problems in patients with PC, causes greater damage in their quality of life 
[20]. The measurement of sleep quality and the evaluation of sleep disorders in patients with PC are very important for the assessment of these individuals holistically, and should be added to the protocol for treating these patients. There is much to clarify about the physiology of the impact of sleep and its disorders, both in normal subjects and in patients with special needs. Forward studies are needed to search for an effective treatment protocol for improvement of quality of life of these individuals.

## Aims and hypotheses

This study aims to assess the sleep variables and masticatory dynamics by means of PSG and EMG, respectively, prior and after neuromuscular electrical stimulation, associated or not with low power laser irradiation (Gallium Arsenide- Aluminun, = 780 nm) and LED (= 660 nm) in patients with cerebral palsy. It is expected that Laser e LED biostimulation will promote the morphophysiologic recovering of muscle fibers and the decreasing of inflammatory process that will be observed through the achievement of muscular physiology within normal patterns established in this study. It is hypothesized that oxyhemoglobin desaturation, caused by pauses in breathing during sleep, can lead to harmful function in neuromuscular system in individuals with CP. We also hypothesize that electrical stimulation, led therapy and laser therapy will contribute to balance the muscular function, adjusting to physiologic patterns of muscular activity, in rest and isometric positions 
[17,18]. The sample will be divided according the randomization rules, in 5 groups with 10 patients (G1,G2,G3,G4,G5). In the G1 will be applied the electrical stimulation, in the G2 laser therapy, in the G3 led therapy, in the G4 the association of led therapy and electrical stimulation and in the G5 the association of laser therapy and electrical stimulation.

## Methods/design

This is a randomized, five arms clinical trial [Figure 
1] conducted according to the ethical standards established in the 1961 Declaration of Helsinki (as revised in Hong Kong in 1989 and in Edimburgh, Scotland in 2000). This study is registered with the World Health Organization Universal Trial Number (UTN) U1111-1123-7969, and Registro Brasileiro de Ensaios Clínicos (RBR-994xfs), and has been approved by the Human Research Ethics Committees of the Universidade Estadual Julio de Mesquita Filho, Sao Jose dos Campos, Brazil (process number 25000.058696/2010-74). All caregivers gave written, informed consent.

**Figure 1 F1:**
[figure not shown]
Flowchart of the study protocol.

## Subjects

Adult individuals between 19 and 60 years old with CP will be recruited from the Training Program in Dentistry for Persons with Disabilities, Department of Biosciences and Oral Diagnosis, School of Dentistry, São Paulo State University, Sao Jose dos Campos, SP, Brazil.

It will be included hemiparetic, quadriparetic or diparetic CP subjects, with partially preserved cognitive function, ability to respond to verbal commands, and informed consent signed by patient or patient’s responsible to voluntary participate in the study. The exclusion criteria are patients underwent to orthodontic or functional maxillary orthopedic treatment and therapies to reduce spasticity (eg. botulinum toxin) at least 6 months before the study.

## Randomization

After the evaluation of the eligibility criteria, the subjects will be randomly distributed into the five intervention groups. Randomization numbers will be generated using envelopes which will contain a card stipulating to which group the subject will be allocated. It will be used sealed and opaque envelopes to ensure confidentiality.

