## Sample size

The sample size, obtained by means of statistical power analysis revealed that with 10 subjects in each group, an 90% power to detect a clinically relevant difference would be present at the alpha level of 0.05.

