## Study interventions

### Clinical evaluation of oromotor functions

Anamnesis will be obtained in order to assess chief complaint, onset, frequency, evolution of the problem, consulted professionals, treatments, results and prescription of drugs, medical and family history, parafunctional habits and psychogenic aspects.

A specific part of the questionnaire will approach sleep breathing disorders, including snoring, choking during sleep, drooling, nightmare experience, movement during sleep and mood after waking. For the clinical examination, dental occlusion, tooth wear, tooth loss, Mallampati evaluation 
[23] and tonsils classification 
[24] will be evaluated. Subjects will also be classified according to the five levels of Gross Motor Function Classification System 
[3]. It is emphasized that oropharyngeal alterations presented in patients with CP will be reviewed by a speech therapist. A modified scale of orofacial motor function assessment for adults with CP, based on Santos 
[25], will be used, in order to evaluate oral motor function, by performing simple movements such as coordination and performance of voluntary facial muscles, jaw protrusion and lateral movement, tongue movements, such as elevation and laterality, lip muscle strength (puff-out cheeks/maintain pressure), glossopharyngeal/hypoglossal motor activity and rapid coordinated jaw, lip, tongue and palatal movement. According to the ability of the patient to perform properly or not each movement, it will be applied the score 0 (inability to perform the movement) to 2 (ability to complete the movement). The sum of scores for each item will result in the total value of the patients oromotor function.

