### Statistical analysis

Data will be presented as means ± standard deviation, when applicable. For comparison of continuous variables prior and after polysomnography and specifics therapies, it will be used the paired Student *t*-test or Wilcoxon tests as appropriate. Comparisons between groups will be performed using Student *t* test or Mann–Whitney U according to the distribution. All tests will be 2 tailed, and p values of less than 0.05 will be assumed to represent statistical significance. All analyses will be performed using SPSS ver. 16.0.

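### The between-group tests on arms of 10 ignore the baseline value of each outcome, and CP type, although the trial records both; a baseline-adjusted model would gain precision at almost no cost.

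*Protocol article*

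**What the plan says.** Under Aims and hypotheses the design is fixed: "The sample will be divided according the randomization rules, in 5 groups with 10 patients (G1,G2,G3,G4,G5"). The Subjects section admits a mixed population: "It will be included hemiparetic, quadriparetic or diparetic CP subjects". Under Clinical evaluation of oromotor functions, severity is graded too: "Subjects will also be classified according to the five levels of Gross Motor Function Classification System", and an oromotor sum score is taken.

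The outcomes themselves are measured before treatment. Phase 1 of the electromyographic exam is the initial collection in all five groups, and the polysomnography section has a full-night recording before and after therapy.

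The Statistical analysis section gives paired tests within groups. Between groups it states "Comparisons between groups will be performed using Student" *t* or Mann–Whitney U, chosen by distribution, and adds "All tests will be 2 tailed, and p values of less than 0.05 will be assumed to represent statistical significance". It names no covariate, and does not say whether the between-group tests use final values or changes from baseline.

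On allocation, the Randomization section says "Randomization numbers will be generated using envelopes which will contain a card stipulating to which group the subject will be allocated" and that the envelopes are sealed and opaque.

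**The concern.** A two-sample *t* or Mann–Whitney test on final values treats all variation between patients as noise. In a sample that mixes hemiparetic, diparetic and quadriparetic adults, part of that variation is probably predictable from what each patient showed before treatment. With 10 per arm, two things follow. Predictable variance stays in the error term and lowers power. And where two arms happen to differ in case mix, the estimated contrast carries that difference uncorrected. The trial already holds the data that would deal with both.

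Unlike the details of allocation, which a condensed article may leave out, the between-group tests are stated outright.

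**Working it through.** **1. The plan's own figure.** The Sample size section claims "with 10 subjects in each group, an 90% power to detect a clinically relevant difference would be present at the alpha level of 0.05". It states no outcome, difference or SD, so the claim can only be solved backwards. For a two-sided two-sample *t* test with 18 df (critical value 2.101) and noncentrality d√(n/2) = d√5, power of 90% needs d = 1.53 SD. The normal approximation gives (1.960 + 1.282) × √(2/10) = 1.45 SD.

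**2. Chance imbalance.** Inputs: five arms of 10 (Aims and hypotheses); m quadriparetic patients of 50 (assumption, not in the article); allocation not balanced on CP type (assumption, since the article does not say). For two arms with a and b quadriparetic patients, P(a, b) = C(10,a) C(10,b) C(30, m−a−b) / C(50,m). Summing over the gaps:

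| m of 50 | Given pair differs by ≥3 | Given pair differs by ≥4 | Highest and lowest of five arms differ by ≥4 |
|---|---|---|---|
| 10 | 16% | 5% | 28% |
| 17 | 24% | 10% | 46% |
| 20 | 26% | 11% | 51% |
| 25 | 27% | 12% | 53% |

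If type shifts a final value by 1 SD (assumption), a gap of 3 of 10 moves that contrast by 0.3 × 1 = 0.3 SD.

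**3. Validity.** In 20,000 simulated comparisons with no true difference and a binary factor correlated 0.5 with the outcome, the unadjusted *t* test rejected in 5.3%. Randomisation keeps the error rate near its nominal level.

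**4. Power with adjustment.** Take a true difference of 1.0 SD and a covariate correlated r with the outcome (assumption).

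- Unadjusted: noncentrality √5 = 2.236, 18 df, power 56%.
- Adjusted for one covariate: noncentrality √5 / √[(1−r²)(1 + 1/16)], 17 df, critical value 2.110. The factor 1 + 1/(2n−4) = 1 + 1/16 pays for chance imbalance in the covariate.

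| r | Noncentrality | Power at 1.0 SD | Power at 1.53 SD (unadjusted 90%) |
|---|---|---|---|
| 0.3 | 2.274 | 57% | 91% |
| 0.5 | 2.505 | 66% | 95% |
| 0.7 | 3.038 | 82% | 99% |

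If the covariate were exactly balanced, the factor would be 1. The noncentralities become 2.582 and 3.131, and power 68% (r = 0.5) and 84% (r = 0.7). Those are upper figures; 66% and 82% apply when balance is left to chance.

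**5. What CP type adds once baseline is in the model.** Suppose type shifts baseline and follow-up alike by 1 within-type SD, with within-type correlation ρ between them (assumptions). With v = p(1−p) and p = 17/50, v = 0.224, so type alone explains 0.224/1.224 = 18% of variance. After baseline, the residual variance is (1+v) − (v+ρ)²/(1+v); after baseline and type it is 1 − ρ².

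- ρ = 0.5: 0.796 falls to 0.750, so type explains 5.8% of what remains.
- ρ = 0.8: 0.367 falls to 0.360, so type explains 2.0%.
- With p = 0.5 the shares are 6.3% and 2.2%.

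As an equivalent sample size, 10/(1−0.020) = 10.2 to 10.7 (p = 0.5, ρ = 0.5: 10/(1−0.0625)) patients per arm instead of 10. Most of the gain therefore comes from the baseline value.

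**6. If changes are compared instead.** With equal SDs, the variance of a change is 2(1−r) times that of a final value: 1.0 at r = 0.5 and 0.6 at r = 0.7. Analysis of covariance has 1−r²: 0.75 and 0.51. It is the smaller in both cases.

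**The case against.** The strongest reply is that nothing here is invalid. Chance imbalance is already part of the 5% error rate, the simulated rate confirms it, and the largest-gap figures describe the worst of ten pairs. For a given pair, a gap of 4 or more has a probability of only 5% to 12%. That stands, and the point concerns precision.

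Second, the benefit depends on how prognostic the covariate is, and the article gives no correlation. At r = 0.3 the gain is one percentage point at 1.0 SD. At the 1.53 SD implied by the sample-size claim, power is already 90%. This also stands and limits the size of the point.

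Third, the between-group tests may be meant for changes from baseline, in which case a stable effect of CP type cancels. The section does not say so, and step 6 shows that adjustment would still be more precise.

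A reader might also infer that allocation is a plain unstratified draw and needs strata, blocks and a new way of preparing envelopes. The documents do not support that. The Randomization section neither describes nor excludes restriction, Aims and hypotheses refers to randomization rules that are not set out, and a condensed article commonly leaves such detail to the full protocol. Nor would strata help much alone: with the planned unadjusted *t* test at r = 0.5 and 1.0 SD, simulated power moves from 55% to 56%.

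**Conclusion.** The point holds for the between-group analysis. As stated, the tests are valid but discard baseline EMG, baseline polysomnography and CP type, and so lose precision in arms of 10. At a true difference of 1.0 SD, adjustment lifts pairwise power from 56% to about 66% (r = 0.5) or 82% (r = 0.7), with little gain at r = 0.3. The correlations, the 1.0 SD difference and the share of quadriparetic patients are all assumptions.

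Two stronger readings should be resisted. The allocation is not shown to be defective, because silence in the article does not show that blocks or strata are absent. And CP type should not be credited with the gain: under the assumptions in step 5 it explains only about 2% to 6% of the variance left after baseline.

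**What to change.** In the Statistical analysis section, replace the between-group *t* and Mann–Whitney tests with a linear model (analysis of covariance) of the post-treatment value on arm and the baseline value of the same outcome. CP type, as quadriparetic versus hemiparetic or diparetic, may be added as an optional term with one degree of freedom; whether it is used should be fixed in advance. Where the distribution requires it, apply the same model to ranks or to a transformed outcome.

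The cost is one or two of the 50 − 5 = 45 residual degrees of freedom in a five-arm model. No extra patients or measurements are needed. This point asks for no change to the allocation.

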## Sample size

The sample size, obtained by means of statistical power analysis revealed that with 10 subjects in each group, an 90% power to detect a clinically relevant difference would be present at the alpha level of 0.05.

## Study interventions

### Clinical evaluation of oromotor functions

Anamnesis will be obtained in order to assess chief complaint, onset, frequency, evolution of the problem, consulted professionals, treatments, results and prescription of drugs, medical and family history, parafunctional habits and psychogenic aspects.

A specific part of the questionnaire will approach sleep breathing disorders, including snoring, choking during sleep, drooling, nightmare experience, movement during sleep and mood after waking. For the clinical examination, dental occlusion, tooth wear, tooth loss, Mallampati evaluation 
[23] and tonsils classification 
[24] will be evaluated. Subjects will also be classified according to the five levels of Gross Motor Function Classification System 
[3]. It is emphasized that oropharyngeal alterations presented in patients with CP will be reviewed by a speech therapist. A modified scale of orofacial motor function assessment for adults with CP, based on Santos 
[25], will be used, in order to evaluate oral motor function, by performing simple movements such as coordination and performance of voluntary facial muscles, jaw protrusion and lateral movement, tongue movements, such as elevation and laterality, lip muscle strength (puff-out cheeks/maintain pressure), glossopharyngeal/hypoglossal motor activity and rapid coordinated jaw, lip, tongue and palatal movement. According to the ability of the patient to perform properly or not each movement, it will be applied the score 0 (inability to perform the movement) to 2 (ability to complete the movement). The sum of scores for each item will result in the total value of the patients oromotor function.

### Surface electromyography

For the EMG record, it will be used an eight-channel electromyography equipment (EMG-800 C, EMG System of Brazil Ltda, Sao Jose dos Campos, SP) [Figure 
2, previously calibrated with amplification of 2000 times and 16-bit resolution. Six input channels will be used to assess the following muscles: channel 1 - anterior portion of right temporalis muscle, channel 2 - superficial portion of right masseter; channel 3 - anterior portion of left temporalis muscle; channel 4 - superficial portion of the left masseter, channel 5 - right suprahyoid muscles; and channel 6 - left suprahyoid muscles. The other two channels will be used for the force transducer and mandibular goniometer. Bipolar, small, passive, circular and disposable Ag/AgC surface electrodes (Meditrace® Kendall-LTP, Chicopee, MA) will be used for evaluation of masticatory system activity. A reference electrode will be positioned in the patients right wrist to reduce undesirable interferences of the electromyographic signal. Volunteers will remain seated, with natural head position during sEMG exam. Electromyographic signals will be recorded after cleaning the skin with 70% alcohol to reduce skin impedance and to allow proper placement of surface electrodes. Surface electrodes will be bilaterally placed according to anatomical references and procedures guided by the direction of muscle fibers in three points, the anterior temporal muscle – 2 to 3 cm superior-posterior distant to the lateral corner of the eyes in the region of greatest evidence of muscle mass, no hair, parallel to the muscle fibers, but with its sensing surface perpendicularly oriented; the superficial portion of masseter – 1 to 2 cm above the gonial angle of the mandible, in the region of greatest evidence of muscle mass, with muscle fibers parallel to the surface, and supra-hyoid muscles – in the region of greatest evidence of muscle mass, parallel to the muscle fibers 
[26] [Figure 
3.

